### 2.3. Exercise Program

Following the parameters obtained during the initial assessment, the physiotherapist will develop a personalized exercise plan tailored to the patient’s needs.

At this stage, the physiotherapy program is designed and learned under the guidance of the physical therapist (2 weeks, 5 sessions per week, 60 min per session) and continued at home daily for three months. During the 10 physiotherapy sessions with the specialist, the patient carefully and correctly learns the exercises to perform at home in the next phase.

The objectives of the exercise program are to correct upper trunk posture, straighten the spinal column, increase mobility, re-educate muscles (by strengthening paravertebral muscles and relaxing muscles in the anterior thoracic area), and prevent or correct secondary axial deviations. Additionally, it aims to improve respiratory function and properly manage breathing during exercise.

The program includes exercises for spinal and rib cage mobility, exercises for toning the extensor trunk muscles (focusing on strengthening the back muscles and relaxing or stretching the front trunk muscles), respiratory re-education exercises, and exercises for stability re-education. To understand the program, Table 1 provides a detailed description of the exercises specifically designed by the authors in a potential work plan.

Proposed exercise plan for patients with PE and secondary axial deviations:

**Table 1 life-15-01624-t001:** Proposed exercise plan for patients with PE.

	Medical Rehabilitation Center	Home Exercise
Exercise Description	Number of Repetitions Week 1–2	Number of Repetitions Week 3–12
***Exercise 1:*** Patient sitting on a Bobath ball, feet on the ground, knee and hip joint, upper limbs placed behind the cervical spine with palms in contact with the cervical spine and arms close to the ear. The patient brings the arms back with an inhale, holds the position for 3–5 s and returns to the starting position with an exhale. (Figure 1a,b)	10 repetitions × 2 sets	10 repetitions × 3 sets
***Exercise 2:*** The patient on the Bobath ball, seated as in the previous exercise, positions the hands under the mandible parallel to the ground, and brings the arms backwards with double extension while inhaling, and then forward while exhaling.	10 repetitions × 2 sets	10 repetitions × 3 sets
***Exercise 3:*** The patient on the Bobath ball, seated as in exercise 1, positions the hands on the shoulders and to perform the exercise brings the arms backwards, forming an imaginary circle, when the arms are parallel to the ground, maintains the position for 3–5 s and returns to the initial position continuing the imaginary circle. (Figure 2a,b)	10 repetitions × 2 sets	10 repetitions × 3 sets
***Exercise 4:*** The patient, sitting with the buttocks on the heels, stretches forward with the hands on the Bobath ball and does trunk extension to stretch the anterior thoracic muscles.	10 repetitions × 2 sets	10 repetitions × 3 sets
***Exercise 5:*** The patient in standing position, upper limbs pointing forward (shoulder flexion 90°), with a 0.5 kg dumbbell in each hand, the exercise requires the sideways movement of one arm at a time, inhaling and back exhaling (Figure 3a,b) an update of the exercise would be to simultaneously extend the arms.	10 repetitions × 2 sets	10 repetitions × 3 sets
***Exercise 6:*** Patient in orthostasis with a cane above the head, positioned horizontally between the two hands, lower the cane to the back pressing on the shoulder blades while inhaling, and back while exhaling.	10 repetitions × 2 sets	10 repetitions × 3 sets
***Exercise 7:*** Patient in orthostasis with a cane positioned horizontally between the two hands, raises the cane overhead while inhaling, and back while exhaling. (Figure 4a,b)	10 repetitions × 2 sets	10 repetitions × 3 sets
***Exercise 8:*** Patient in orthostasis, arms extended parallel to the floor, the exercise involves extending the trunk while lifting the arms and legs off the floor.	10 repetitions × 2 sets	10 repetitions × 3 sets
***Exercise 9:*** Patient in prone position, arms stretched, holding a cane, the exercise involves pulling the cane to the chest with slight extension of the spine + inhaling, return to the initial position on exhaling (Figure 5a,b)	10 repetitions × 2 sets	10 repetitions × 3 sets
***Exercise 10:*** Aerobic training: stationary cycling in order to increase exercise tolerance, increase energy intake.	15 min	20 min

### 2.4. Measurements

In the first stage, we conduct investigations to establish the patient’s sample, and the physiotherapist designs a personalized physiotherapy program. This is followed by the second stage, where the physiotherapy program is carried out and learned under the guidance of the specialist. The final stage involves re-evaluating the patient after completing the physiotherapy program and drawing conclusions from the study.

Each parameter will be reviewed by the investigators, documented in an Excel file, and then their correlation will be analyzed using a statistical program.

In the initial phase after establishing the two samples, evaluation of each subject begins as follows: myotonometric assessment of the involved muscles (Trapezius muscle with all three fascicles, Pectoralis Major muscle), on both the left and right sides, along with cardiopulmonary exercise testing (CPET), postural analysis (GaitOn), and static balance measurement (stabilometry-PoData), using non-invasive tests.

#### 2.4.1. Myotonometry

The myotonometer offers an objective method to measure the physiological properties of muscle tone. The MyotonPRO is a compact, portable, non-invasive myotonometer that provides an objective measurement of the mechanical properties of muscle [18].

The device simultaneously measures or calculates five parameters, divided into three sections: the first section assesses the muscle’s tension state by measuring the natural oscillation frequency [Hz], which reflects the muscle’s tension. The second section includes biomechanical properties such as dynamic stiffness [N/m] and logarithmic decrement, which characterize muscle elasticity. The third section covers viscoelastic properties of the muscle, with the device recording results on the mechanical stress relaxation time [ms] and the ratio of relaxation time to deformation time, indicating CREEP (Deborah number) [19].

The device is set for a specific target group and follows an internal protocol based on the muscles involved in the test. After introducing a new subject, the established protocol is loaded onto the device to begin the test.

For testing, the patient must be seated on a chair, and according to the established protocol, testing is performed bilaterally, always starting with the left side in the following order: pectoralis major (Figure 6a,b, measured 5 cm above the nipple), upper trapezius (Figure 7a,b, perpendicular to the muscle fibers at the midpoint between the lateral cervical line and the acromion), middle trapezius (Figure 8a,b, halfway between the spine and the medial border of the scapula at T3 level), and lower trapezius (Figure 9a,b, 3 cm medial and inferior to the inferior angle of the scapula, on the line between the scapula and the spine). To perform the test, touch the external end of the device to the central part of the muscle belly and wait for five direct pulses (each indicated by a green light). If the results are written in red, repeat the test on that muscle until the results turn white. After completing the test, upload the results to the laptop and then export them to a separate Excel document for statistical analysis.

#### 2.4.2. Cardiopulmonary Exercise Testing (CPET)

Assessment of cardiopulmonary condition will be performed with the BTL-CPET device, which uses glue-wired electrodes that are attached by a cable to a portable EKG device mounted around the patient’s abdomen [20].

Blood pressure should be measured at the beginning and at the end of the test. Alternatively, a blood pressure cuff may be attached to the patient’s arm. Additionally, a pulse oximeter will be worn on the patient’s finger to monitor tissue oxygen levels and heart rate.

A mask that attaches to the head with a rubber band is used for lung testing. It must be sealed so the person breathes only through the opening in the mask. A cylinder is inserted into the hole in the mask and connected by wires to an air filter. The filter provides data on the amount of oxygen inhaled and the amount of carbon dioxide exhaled.

Once the preparations are complete, the patient is asked to step onto the treadmill to start testing. This begins with a 3 min warm-up period during which the patient is asked to walk. After the warm-up, the actual testing begins. Each level has a specific incline and speed, which increase gradually during the test (Figure 10).

The study uses the modified Bruce Protocol, which starts at a speed of 1.7 mph and a 0% incline. The second and third stages maintain the same speed, but the slope increases by 5% in each stage. Each subsequent stage increases in speed by 1.12 to 1.28 km/h and in incline by 2%. The test lasts approximately 10 to 13 min, followed by a 3 min recovery period [21].

With cardiopulmonary exercise testing, we gather data on the body’s response to both maximal and submaximal exercise by recording cardiac parameters (electrocardiogram) and respiratory parameters. Depending on the respiratory gases, we calculate VE and VO_2max_ [22].

Endurance capacity indicators include maximal oxygen consumption (VO_2_) and ventilation thresholds (VT1 and VT2). Additionally, anaerobic capacity, movement economy, and mechanical efficiency can also be assessed through gas exchange measurements, while cardiopulmonary exercise testing helps define exercise intensity zones.

#### 2.4.3. Static Balance

Stabilometric assessment will be conducted using the Chinesport device (PoDATA 2.0) [23]. The device measures body mass distribution at three points for each foot: the first and fifth metatarsal heads and the heel (Figure 11a–c). For the assessment, the patient is asked to remove their shoes. After the device is calibrated, the patient walks on the test surface, maintaining upright posture and performing various movements as directed by the coordinator. The evaluation includes the following tests, each lasting 20 s: eyes open, eyes closed, head rotated to the right or left, head tilted laterally to the right or left, and head in hyperextension. Each test is performed to observe how the center of gravity balances during different movements performed throughout the day, helping us understand how the PE affects stability.

#### 2.4.4. Evaluation of Posture (GaitOn)

Evaluation of patients’ posture and body alignment will be carried out using the GaitON Posture Analysis System, which assesses the patient’s posture from anterior, posterior, right, and left views. It identifies key postural deviations from multiple angles and calculates a ratio of the deviations [24].

The patient is evaluated from four perspectives. Anterior view: Markers are placed at the earlobe, anterior superior iliac crest, midpoint of the patella, and on the tibial tuberosity, on both the right and left sides (Figure 12a). Posterior view: Markers are placed at the base of the calcaneus, where the Achilles tendon inserts, the center of the Achilles tendon, and mid-calf. (Figure 12b) Lateral left-right view: Markers are positioned at the C7 spinous process, midpoint of the humeral head, greater trochanter of the femur, lateral epicondyle of the femur, and lateral malleolus (Figure 13a,b).

To test after applying the markers, the patient is photographed from four angles (anterior, posterior, and lateral views on both the left and right sides). The photographs are entered into a system, and after analysis, a report is generated documenting and illustrating the associated axial deviations involved [24].

### 2.5. Statistical Analysis

Statistics will be performed using GraphPad Prism 5.0 for Windows. The descriptive statistics will be computed for all variables (mean and standard deviation). Before statistical applications, the normal distribution of values will be verified by the D’Agostino-Pearson normality test. The intragroup data (analyzed parameters at baseline and after the physical exercise program) will be compared with the paired *t*-test.

For the myotonometry, frequency, stiffness, decrement, stress relaxation time and creep of the trapezius and major pectoralis will be compared before and after the 3-month physical exercise program. VE and VO_2max_ will be analyzed at baseline and after the physical exercise program. Paired *t*-tests will be used to compare the intragroup data of the postural stability parameters (stabilometry data in the different testing situations). GaitOn postural analysis parameters will be measured before and after the 3-month physical exercise program.

## 3. Expected Results

Based on the hypothesis of our study, we expect changes in the parameters of the four assessments (myotonometry, stabilometry, postural analysis, and cardiopulmonary exercise testing) when comparing baseline data with the 3-month results. A difference in myotonometric parameters is anticipated between the concave (anterior thoracic) muscles and the Trapezius muscle, specifically in resting tone, stiffness, elasticity, and muscle relaxation time. Additionally, differences between the initial and 3-month evaluations are expected for the biomechanical and viscoelastic properties of the Trapezius and Pectoralis muscles.

We also expect differences between the baseline and the 3-month assessment in the GaitOn analysis parameters. Changes are anticipated in the lateral view examinations. The shoulder angle, with improved values, is targeted after the 3-month exercise program.

In terms of cardiopulmonary assessment, significantly positive differences are expected regarding the patient’s ability to manage breathing times (inhale and exhale) during exercise.

From a clinical perspective, we expect an overall improvement in the appearance and function of the chest, better posture, and potentially relief from some symptoms related to the condition.

Regarding stabilometry, the goal is to understand the differences and possible correlations of the resulting values after correcting posture and shifting the center of gravity. We anticipate improved postural stability in patients following the 3-month physical exercise program.

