### 2.1. Sample Size Calculation

The effect size was 0.5, the type I error was α = 0.05, and power was 0.8. A total sample size of at least 35 patients was required. The sample size was calculated using G*Power 3.1.9.7 (Universitat Kiel, Kiel, Germany) with the Wilcoxon signed-rank test (matched pairs)

The within-group analyses will evaluate the effects over time. The evaluation of effect size was based on Cohen’s conventions for large effects [14]. The total sample size of our study (at least 35 patients) is in accordance with that calculated by Zielinski for patients who followed kinesiotherapy with the same statistical power and effect size (36 patients) [15].

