## 4. Discussion

The study will be randomized and will examine the characteristics of the trapezius and pectoralis major muscles, respiratory function, stability, and overall posture in children and adolescents with PE before and after a tailored physical therapy program lasting three months. The assessment of study participants will include four different testing methods: myotonometry, cardiopulmonary exercise testing (CPET), posture evaluation, and static balance analysis.

An excessively high position in the upper chest area may cause PE, and the pectoralis major muscle has a biomechanical role in lifting the sternum [25]. Consequently, the main hypothesis of this investigation will focus on assessing the tone of the pectoralis major and trapezius muscles, as well as examining any recorded discrepancies that might contribute to this condition. The study will explore changes in length, elasticity, muscle tone, and relaxation in muscles potentially involved in the development of the pathology through a non-invasive measurement method: myotonometry. No studies have been found in the literature that evaluate the properties of muscles involved in the development of PE. However, some evidence links thoracic kyphosis with this condition [6], prompting an analysis of the literature’s reported changes and a comparison with the findings of this study. Thoracic kyphosis appears as limited mobility of the thoracic spine caused by alterations in both non-contractile and contractile tissues [26].

Therefore, in a study conducted by Yeo et al., muscle tone was evaluated in the upper trapezius and pectoralis major muscles of patients with thoracic kyphosis using MyotonPro^®^ (Myoton AS, Tallinn, Estonia). Variations in the examined parameters were observed [27]. The measurement technique used in this study is similar to that in our research, with the MyotonPRO^®^ tip positioned vertically at the midpoint of the subjects’ upper trapezius and pectoralis major muscles.

The CPET evaluation of the study participants will assess the effect of sternal deformity on cardiopulmonary function and compare the results with those reported in existing literature.

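### The anticipated pectoralis-trapezius difference has no matching analysis: Section 2.5 plans only before-after tests within each muscle

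*Protocol article*

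**What the plan says.** Section 3 (Expected Results) sets out two myotonometric expectations. The first compares muscles: "A difference in myotonometric parameters is anticipated between the concave (anterior thoracic) muscles and the Trapezius muscle", and it names resting tone, stiffness, elasticity and relaxation time. The second, added as a separate item, is a change from baseline to three months in both muscles.

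Section 4 (Discussion) says that "the main hypothesis of this investigation will focus on assessing the tone of the pectoralis major and trapezius muscles", and adds that recorded discrepancies which might contribute to the condition will be examined. Section 2 instead gives respiratory function and body posture as the main objective.

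Section 2.5 states the myotonometry analysis: "frequency, stiffness, decrement, stress relaxation time and creep of the trapezius and major pectoralis will be compared before and after" the three-month programme. The method is general to all outcomes: "The intragroup data (analyzed parameters at baseline and after the physical exercise program) will be compared with the paired" t-test. Section 2.1 sizes the study for the same purpose: "The within-group analyses will evaluate the effects over time". Beyond descriptive means and standard deviations, the only other analysis mentioned is an unspecified correlation of the parameters (Sections 2.4 and 4).

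**The concern.** The article states an expectation about two muscles and separately states the analysis of those muscles, and the second does not answer the first. A before-after test in pectoralis major and another in trapezius each ask whether that muscle changed. Neither asks whether the muscles differ, at baseline or in how they change.

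Two misreadings become possible. If one muscle changes significantly and the other does not, this may be reported as a different response, which two separate p-values cannot show. If the muscles differ at baseline, this may be reported as a discrepancy contributing to pectus excavatum. Two different muscles may well differ in any child, and the article describes no healthy comparison group against which to judge the gap.

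The contrast is also informative in its own right. Section 2.3 sets different aims for the two regions (strengthening the back, relaxing the front of the chest), so a differential change would be a natural signature of the programme. In a one-group before-after analysis it would also remove any time effect that is equal in both muscles.

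**Working it through.** **What each analysis estimates.** Write P0, P1 for a pectoralis parameter before and after, and T0, T1 for the same trapezius parameter.

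- Planned in Section 2.5: the mean of P1 − P0, and separately the mean of T1 − T0.
- Difference in level: the mean of P0 − T0 (or P1 − T1). The two mean changes carry no information about it.
- Difference in change: the mean of (P1 − P0) − (T1 − T0). Its estimate is the gap between the two mean changes, but its standard error depends on their correlation within children, and no test of it is planned.

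**The plan's own figure.** Section 2.1 gives these inputs: "The effect size was 0.5, the type I error was α = 0.05, and power was 0.8". The test is the matched-pairs Wilcoxon signed-rank test, and the answer reported is 35. Sidedness is not stated. Taking it as two-sided, with a normal parent and relative efficiency 3/π:

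- effective n = 35 × 3/π = 33.4
- noncentrality = 0.5 × √33.4 = 2.89
- power = 0.801, and 35 is the smallest n that reaches 0.80.

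The stated 35 is reproduced. It covers a change over time in one measure and no between-muscle contrast. The planned paired t-test with the same inputs has power 0.82 at n = 35.

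**Separate tests when both muscles change equally.** The correlation ρ between the two changes is not in the documents, so 0 to 0.7 is assumed. The 0.5 SD change borrows the effect size of Section 2.1; 0.35 SD is an assumption. Simulation: 40,000 trials per setting, n = 35, two-sided 0.05, bivariate normal changes. Share of trials in which exactly one of the two tests is significant:

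| True change in both | ρ = 0 | 0.3 | 0.5 | 0.7 |
|---|---|---|---|---|
| 0.35 SD | 50% | 41% | 34% | 26% |
| 0.5 SD | 30% | 25% | 22% | 17% |

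Hand check at 0.5 SD and ρ = 0: 2 × 0.82 × 0.18 = 0.30. The direct within-child test of the difference in change was significant in about 5% of trials in every setting, as it should be.

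**Power of the direct contrast.** Suppose one muscle changes by 0.5 SD and the other not at all, with equal SDs of change and one measure per muscle. The standardised effect is then 0.5 / √(2(1 − ρ)).

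| ρ | Effect | Power at n = 35 | n for 80% power |
|---|---|---|---|
| 0 | 0.354 | 0.53 | 65 |
| 0.3 | 0.423 | 0.68 | 46 |
| 0.5 | 0.500 | 0.82 | 34 |
| 0.7 | 0.645 | 0.96 | 21 |

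The contrast matches the single-muscle test (0.82) at ρ = 0.5. It is weaker below that and stronger above.

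**The case against.** The strongest reply is that the Section 3 sentence most naturally describes a difference in level, since change over time follows as a separate expectation. On that reading no differential change is hypothesised and the discordance figures do not apply. This stands as a limit on the figures. It does not close the gap, because before-after tests are silent on level too. Means and standard deviations will describe each muscle's level but are not a within-child comparison.

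A reader might infer that the investigators will judge a differential response by comparing the muscles' p-values. The article says no such thing. The risk arises only if a differential response is claimed from the tests listed.

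A reader might also infer that a pectoralis-trapezius difference is the main hypothesis. The Discussion says the hypothesis focuses on the tone of these muscles and on discrepancies. It does not say discrepancies between the muscles; left-right differences or differences from the literature would also fit. Section 2 gives another main objective.

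A condensed article may leave exploratory contrasts to a plan that is not shown. That would excuse silence. Here, however, Section 2.5 names the muscles, parameters and comparison, and that comparison does not match the stated expectation.

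Three technical limits also stand. Equal change in both muscles is an illustrative null, not what the programme aims for. Only time effects that are equal in both muscles cancel; growth specific to one muscle, or drift proportional to level, does not. Section 2.4.1 measures three trapezius fascicles separately, and averaging them could hide opposite changes.

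**Conclusion.** The point holds as a mismatch within the article: a between-muscle difference is anticipated, and the stated analysis cannot test it on either reading. The before-after tests are sound for the question they do answer, and the sample size of 35 is correct for its own inputs.

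If a differential change were claimed from separate tests, they would disagree in about 17% to 50% of trials with identical true changes, against about 5% false positives for the direct contrast. With only one muscle changing by 0.5 SD, the contrast has power 0.53 to 0.96. Both ranges assume correlations of 0 to 0.7, and the power range also assumes single measures with equal SDs. The exact contrast recommended below, with several fascicles and two sides, was not modelled. The gap should be fixed before analysis, but it does not undermine the before-after comparisons.

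**What to change.** 1. In Section 3, state whether the anticipated difference concerns level, change or both, and align the Discussion's main hypothesis with the main objective in Section 2.
2. In Section 2.5, add one within-child contrast per myotonometric parameter with a 95% confidence interval. One suitable form is a mixed model with muscle, visit and muscle-by-visit terms and a random effect for child: the muscle term addresses baseline level and the interaction addresses change. Keep the trapezius fascicles separate or justify averaging them, and say how the two sides are handled.
3. State that separate per-muscle p-values will not be used to claim that the muscles respond differently.
4. State that a baseline difference between two different muscles, without a healthy comparison group, will not be read as contributing to pectus excavatum.

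The cost is analysis wording, since both muscles are already measured bilaterally and analysed before and after. The downsides are lower power than a single-muscle test when the changes are weakly correlated, and protection only against time effects that are equal in both muscles.
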